### Relevant concomitant care permitted or prohibited during the trial {11d}

The current study targets healthy adults unlike clinical trials that involve clinical populations. Hence, there are no alternative interventions for participants. Nonetheless, to ensure that any observed effects can be unequivocally attributed to the Structure Learning training programme, participants are asked to avoid engaging in any other intervention studies or brain stimulation research during their study involvement. We will proceed to withdraw a participant once we know that they are concurrently involved in other intervention studies or brain stimulation research to maintain the integrity of the data.

### Provisions for post-trial care {30}

We anticipate minimal harm to participants as the current study primarily involves cognitive training and tasks. However, we acknowledge that mental fatigue may arise with multiple experiment sessions that can span up to 3 h. Furthermore, our MRI scans are also longer than usual scans due to the sequence run. Thus, we enforce compulsory breaks during all experiment sessions whenever possible and participants are also allowed to take additional breaks during the sessions. Participants can also choose to withdraw from the study at any point in time. Even though MRI is in general a safe technique, the exposure of participants to a strong magnetic field can lead to minor side effects such as tingling sensations in the limbs or vertigo. Experimenters will closely monitor and follow-up on participants’ well-being after each MRI session. Serious adverse events will be reported promptly to the university’s IRB for appropriate action. Researchers may also unintentionally discover information about participants’ health conditions from their brain scans. Any brain structural anomalies observed will be raised to the principal investigators as incidental findings and reviewed by medical professionals. Barring any life-threatening medical issues, we only notify participants of any incidental findings if they indicate that they would like to be notified. The principal investigator(s) and/or qualified medical personnel(s) will explain the findings to the participants.

### Outcomes {12}

In the present study, multiple behavioural tasks are administered to measure various cognitive constructs. Primary behavioural constructs under investigation include Structure Learning, cognitive flexibility, inhibition, and working memory. Secondary behavioural constructs under investigation include creativity, intelligence, problem-solving, language skills, numeracy skills, social tendencies, and decision making. These measures are conducted only at pre-test assessment, i.e. baseline, only at post-test assessment, i.e. after the end of structure learning training and approximately 2 months from pre-test assessment, or at both pre-test and post-test assessments. Specifically, we administered secondary behavioural constructs measuring language skills, numeracy skills, and intelligence (with the exception of the Raven’s Advanced Progressive Matrices) only at pre-test assessments as they are traits that remain relatively stable across the adult lifespan. We administered primary and secondary behavioural constructs measuring cognitive flexibility (with the exception of the Colour Shape Task), inhibition, working memory, creativity, and problem-solving only at post-test assessments to eliminate possibility of practice effects. Finally, matching tasks, i.e. Colour Shape Task and Raven’s Advanced Progressive Matrices, secondary behavioural constructs that measure social tendencies and decision making (and hence more impervious to practice effects) and all secondary neuroimaging constructs are measured at both pre and post-test assessments. Both the Control and Training groups undergo the same measures at pre and post-test assessments. However, measures for Structure Learning are collected only for the Training group. In addition, we investigate potential neural benefits of the Structure Learning training by assessing secondary neuroimaging outcomes both structurally and functionally. Detailed information regarding the individual tasks used this study can be found in Appendix B in the supplementary information.

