### Objectives {7}

The primary aim of the present study is to investigate whether a novel cognitive training programme based on Structure Learning can improve cognitive flexibility performance in a healthy adult population. The near-transfer benefits of the training are first evaluated within the Structure Learning task itself. We will investigate how participants adapt their behaviour in response to new stimuli and learning rules introduced intermittently throughout the training programme. We hypothesise that participants who undergo Structure Learning training will demonstrate the ability to apply previously extracted rules from their training sessions to these novel training elements. Secondly, near-transfer benefits are assessed within the CF construct using common tasks that measure CF performance. We anticipate significant improvements in CF performance among participants who underwent the cognitive training programme (Training group), in comparison to those who did not go through the programme (Control group).

The secondary aim of the study is to comprehensively assess potential behavioural and neural changes that may emerge from the cognitive training programme on a pilot level. We aim to investigate far-transfer benefits of the training across a wide range of socio-cognitive behaviours which includes working memory, inhibition, creativity, problem-solving, decision making and socioemotional skills. The Structure Learning task fundamentally taps onto the mechanism of statistical learning which underlies any learning or cognitive ability that involves probabilistic build-up of experiences or expectations. Hence, based on the ubiquity of the ability that the Structure Learning training programme aims to train, we hypothesise that we will see far-transfer benefits in at least one of the socio-cognitive domains that we are examining.

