### Trial design {8}

Participants are recruited in batches consisting of up to 18 individuals. To establish a baseline, each batch of recruited participants undergoes a cognitive session that assesses their verbal and non-verbal intelligence, and baseline cognitive flexibility performance. Following the baseline assessment, participants are assigned to either the (1) Training group (receiving Structure Learning training) or (2) Control group (serving as a passive control without any training) using a parallel assignment method. The allocation ratio is set at 1:1 to ensure an equal distribution of participants between the two groups. Group assignment follows procedures of a randomised controlled trial but with matching constraints of age, sex, intelligence, and baseline cognitive flexibility performance between groups. Measures of executive functions can be susceptible to practice effects which can confound the study outcomes [42]. We circumvent this issue by administering most primary and secondary measures only at the post-test to both Training and Control groups. Therefore, matching the groups in the aforementioned variables is important so that we can compare critical outcome measures of the two groups at post-test to examine the effects of the Structure Learning training programme. Consequently, the study is designed as a superiority trial with the aim of demonstrating that the performance of the Training group that engages in the Structure Learning training programme will be superior to that of the Control group for primary outcome measures administered at post-test.

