#### Primary outcomes

(1) Cognitive flexibilityMeasuring cognitive flexibility poses a significant challenge due to the multitude of ways in which it has been defined and measured in previous research. In the present study, cognitive flexibility is operationalised by incorporating both set shifting and task switching behavioural paradigms. These paradigms have been widely utilised in numerous studies to investigate cognitive flexibility (for reviews [46, 47]). Although both set shifting and task switching taps onto cognitive flexibility, they invoke slightly different cognitive processes. In set shifting, participants are typically presented with the same stimuli sets throughout the task, which consist of two or more features. To successfully complete the task, participants must dynamically shift their attention between these features, generating different rules that enable them to effectively follow the overall instructions and solve the task. To investigate set shifting ability, the Wisconsin card sorting test (WCST), intra/extra-dimensional set shifting, and probabilistic reversal learning tasks are used. In task switching, participants are similarly presented with the same stimuli throughout the task but instead, explicitly asked to switch between tasks with different instructions. We used the task set switching where, task set switching what, colour shape task (CST), and trail making test to investigate task switching ability. Both conventional measures and modelling parameters will be derived from these tasks for further analyses.(2) Working memoryThe working memory component in the executive function framework derived by Friedman and Miyake[25] pertains more to the processing control and updating capabilities within working memory instead of its temporary storage capabilities. Hence, tasks chosen to investigate this updating aspect commonly necessitate additional processing of the encoded information. We chose three tasks to investigate working memory updating in the present study. In backwards digit span (BDS), participants are presented with an auditory stream of digits then asked to repeat them backwards. In the reading span task, a dual task paradigm is used, and participants have to alternate digits and sentence judgement which also invokes processing and updating capabilities of the working memory. In the Cambridge neuropsychological test automated battery (CANTAB) version of the spatial working memory task, participants are asked to continuously update spatial information encoded in their working memory as the task progresses to solve the task.(3) InhibitionInhibition in the context of the executive function framework refers specifically to the ability to exercise control over one’s behaviour through overriding a prepotent and automatic response. Inhibition or response inhibition is particularly pivotal in the regulation of goal-directed behaviours. In the present study, inhibition is measured with the Stroop task and the stop-signal task.(4) Structure learningStructure learning is the training component of this study assessing through multiple measures. Contingency learning in participants is quantified as a performance index (PI) that reflects the comparison of participant’s response distribution with presented target distribution across the training. In addition, the types of strategy used by participants are also quantified with strategy choice and the strategy integral curve difference (strategy ICD). These variables are further used to examine the rate of change of learning and strategy across training sessions. Detailed calculations of these measures are included in the statistical plan.

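### Working memory and inhibition are secondary far-transfer domains in Objectives but primary in Outcomes, and the superiority claim over 12 between-group tasks names no deciding measure

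*Protocol article*

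**What the plan says.** All references are to the protocol article.

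- **Objectives {7}.** The primary aim is improvement in cognitive flexibility. It has two parts: transfer within the Structure Learning task, then better performance than Control on common flexibility tasks. The next aim is introduced with "The secondary aim of the study is to comprehensively assess potential behavioural and neural changes" and is set at pilot level. Its far-transfer domains are listed in words "which includes working memory, inhibition, creativity, problem-solving, decision making and socioemotional skills". The hypothesis for this aim is that "we will see far-transfer benefits in at least one of the socio-cognitive domains that we are examining".
- **Outcomes {12}.** "Primary behavioural constructs under investigation include Structure Learning, cognitive flexibility, inhibition, and working memory". The same section says that Structure Learning measures are taken in the Training group only.
- **Primary outcomes.** For set shifting, "the Wisconsin card sorting test (WCST), intra/extra-dimensional set shifting, and probabilistic reversal learning tasks are used". Four task-switching tasks, three working-memory tasks and two inhibition tasks are also named. The flexibility paragraph ends: "Both conventional measures and modelling parameters will be derived from these tasks for further analyses".
- **Secondary behavioural outcomes.** These are described as mainly the far-transfer outcomes, but Table 2 contains neither working memory nor inhibition.
- **Trial design {8}.** The trial is a superiority trial, to show that the Training group's performance "will be superior to that of the Control group for primary outcome measures administered at post-test".
- **Evaluation of efficacy of Structure Learning training.** Individual primary outcomes are compared between groups with parametric tests where possible. In addition, combinations of measures chosen from a concurrent study's structural equation model are analysed in a multivariate mixed effects model.
- **Sample size {14}.** This gives the only type I error rate in the article, 0.05.

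**The concern.** Two sections give the same constructs different standing. Under Outcomes {12} and Trial design {8}, a group difference on backwards digit span or the Stroop task is evidence for the superiority claim. Under Objectives {7}, it is a pilot-level far-transfer result. Neither a reader nor an analyst can tell from the article which applies.

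The superiority claim also has no stated target: no lead measure, and no rule that all, any or a given number of the primary measures must succeed. With many candidates and no rule, the measure that carries the claim can be chosen after the results are seen. This matters more here because, under Who will be blinded {17a}, analysts know the group assignment and the stated protection against bias is that hypotheses are set in advance. That protection works only if the main hypothesis is unambiguous.

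Sample size {14} says the study should inform the size of later studies. An effect picked as the largest of several would overstate what those studies should expect.

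**Working it through.** **1. Is there a contradiction?**

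| Construct | Objectives {7} | Outcomes {12} and Primary outcomes | Table 2 (secondary) |
|---|---|---|---|
| Cognitive flexibility | Primary aim | Primary | Absent |
| Working memory | Secondary aim, far transfer | Primary | Absent |
| Inhibition | Secondary aim, far transfer | Primary | Absent |
| Structure Learning | Primary aim, within-task transfer | Primary, Training group only | Absent |

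Working memory and inhibition conflict. Structure Learning is consistent across sections, but it cannot be compared with Control.

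**2. How many between-group primary tasks are there?** From Primary outcomes: 3 set-shifting + 4 task-switching = 7 flexibility tasks; 3 working memory; 2 inhibition. 7 + 3 + 2 = 12. This is a minimum, since the flexibility tasks yield more than one measure.

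**3. What error rate would 12 unadjusted tests carry?** The article gives no family-wise figure to reproduce. Assumptions: no true effect on any task; each test two-sided at 0.05; no adjustment; any significant task counts. The between-task correlation is not given, so a range is shown.

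Under independence:
- Either direction: 1 − 0.95^12 = 1 − 0.540 = 0.460.
- Favouring Training (2.5% per test): 1 − 0.975^12 = 1 − 0.738 = 0.262.

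With equally correlated normal test statistics (simulation, 400,000 draws):

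| Correlation | Either direction | Favouring Training |
|---|---|---|
| 0 | 46% | 26% |
| 0.3 | 40% | 20% |
| 0.5 | 32% | 16% |
| 0.7 | 23% | 12% |

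The nominal rates for a single test are 5% and 2.5%. The seven flexibility tasks alone give 1 − 0.95^7 = 30% in either direction under independence, so moving working memory and inhibition does not by itself solve the problem.

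**4. The far-transfer hypothesis.** Six domains, one test each at 0.05, independent: 1 − 0.95^6 = 1 − 0.735 = 0.265 in either direction, and 1 − 0.975^6 = 1 − 0.859 = 0.141 favouring Training. At correlation 0.3 these are 24% and 12%.

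**5. Why not simply adjust over 12 tasks?** Bonferroni gives 0.05 / 12 = 0.00417 per test. At 50 per group and an assumed standardised difference of 0.5 at post-test, power falls from 0.71 to 0.36, and about 110 per group would be needed for 80%. A single composite tested at 0.05 avoids that penalty.

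**The case against.** **The study is close to a pilot.** Sample size {14} calls it a scoping study, and the choice-of-comparator section says it approaches a pilot. That softens the consequences. However, Trial design {8} declares a superiority trial, and Sample size {14} plans it at 0.05 with 80% power. The contradiction in classification remains either way.

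**A multiplicity rule may exist elsewhere.** This stands. The article does not say that the tasks share one alpha or that no adjustment will be made. The 0.05 appears only in the sample-size paragraph, and a rule may sit in an analysis plan that is not shown. The error rates are therefore conditional. An analysis plan could not, however, settle the status of working memory and inhibition without departing from one of the sections.

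**Objectives may be the outlier.** The abstract's focus on executive functions and the efficacy section agree with Outcomes {12}. That is a fair argument for reconciling in the other direction. The flexibility aim is nevertheless the only between-group aim that Objectives calls primary.

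**A combined analysis is already planned.** It is, but in addition to the individual comparisons and with no stated priority over them.

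Four stronger readings are not supported:
- *That a false success is likely.* For 12 tasks, the chance of a false result favouring Training is 12–26%.
- *That one significant domain makes the trial a success.* The at-least-one wording is a hypothesis for the secondary aim, not a decision rule for the primary tasks.
- *That all 12 tasks contribute both conventional and model-based measures.* That sentence closes the flexibility paragraph and covers its seven tasks only.
- *That Structure Learning is wrongly primary.* Objectives puts within-task transfer in the primary aim, and Outcomes {12} discloses that only the Training group provides it.

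**Conclusion.** The point holds as an internal contradiction with an undefined superiority target. Working memory and inhibition are secondary in one section and primary in another, and nothing in the article says which of at least 12 between-group tasks decides the claim.

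The size is conditional. With unadjusted two-sided tests at 0.05, and any one significant task counted as success, the family-wise error is 23–46% in either direction and 12–26% favouring Training, for assumed correlations from 0.7 down to 0. Read without adjustment, the six-domain far-transfer hypothesis carries about 26% under independence, or 14% favouring Training. These figures show what the wording permits; they do not show that the sponsor intends to analyse the data this way. The contradiction itself rests on none of these assumptions. It should be corrected before outcome data are analysed.

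**What to change.** Reconcile Objectives {7}, Trial design {8}, Outcomes {12}, Primary outcomes, Secondary behavioural outcomes with Table 2, and the efficacy section, as follows:

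1. Rest the superiority claim on one cognitive-flexibility composite, tested at 0.05. Use the combination already planned in the efficacy section, with its component measures and weights frozen before outcome data are analysed.
2. Classify working memory and inhibition as secondary, as in Objectives, and list them with the other secondary outcomes.
3. Replace an unadjusted reading of the at-least-one hypothesis with one test for each of the six far-transfer domains, in a single Holm family. Working memory and inhibition each enter once. The smallest p-value is compared with 0.05 / 6 = 0.0083. One summary measure per domain must be named in advance.
4. Report individual tasks with confidence intervals as supportive results.
5. Keep Structure Learning as the within-Training part of the primary aim, and state that the superiority claim does not cover it because Controls do not perform the task.

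Cost: changes of wording, fewer nominally significant results, and the loss of primary status for working memory and inhibition. The concurrent study's model must be settled in time to fix the weights. No new data are needed.

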#### Primary outcomes

(1) Cognitive flexibilityMeasuring cognitive flexibility poses a significant challenge due to the multitude of ways in which it has been defined and measured in previous research. In the present study, cognitive flexibility is operationalised by incorporating both set shifting and task switching behavioural paradigms. These paradigms have been widely utilised in numerous studies to investigate cognitive flexibility (for reviews [46, 47]). Although both set shifting and task switching taps onto cognitive flexibility, they invoke slightly different cognitive processes. In set shifting, participants are typically presented with the same stimuli sets throughout the task, which consist of two or more features. To successfully complete the task, participants must dynamically shift their attention between these features, generating different rules that enable them to effectively follow the overall instructions and solve the task. To investigate set shifting ability, the Wisconsin card sorting test (WCST), intra/extra-dimensional set shifting, and probabilistic reversal learning tasks are used. In task switching, participants are similarly presented with the same stimuli throughout the task but instead, explicitly asked to switch between tasks with different instructions. We used the task set switching where, task set switching what, colour shape task (CST), and trail making test to investigate task switching ability. Both conventional measures and modelling parameters will be derived from these tasks for further analyses.(2) Working memoryThe working memory component in the executive function framework derived by Friedman and Miyake[25] pertains more to the processing control and updating capabilities within working memory instead of its temporary storage capabilities. Hence, tasks chosen to investigate this updating aspect commonly necessitate additional processing of the encoded information. We chose three tasks to investigate working memory updating in the present study. In backwards digit span (BDS), participants are presented with an auditory stream of digits then asked to repeat them backwards. In the reading span task, a dual task paradigm is used, and participants have to alternate digits and sentence judgement which also invokes processing and updating capabilities of the working memory. In the Cambridge neuropsychological test automated battery (CANTAB) version of the spatial working memory task, participants are asked to continuously update spatial information encoded in their working memory as the task progresses to solve the task.(3) InhibitionInhibition in the context of the executive function framework refers specifically to the ability to exercise control over one’s behaviour through overriding a prepotent and automatic response. Inhibition or response inhibition is particularly pivotal in the regulation of goal-directed behaviours. In the present study, inhibition is measured with the Stroop task and the stop-signal task.(4) Structure learningStructure learning is the training component of this study assessing through multiple measures. Contingency learning in participants is quantified as a performance index (PI) that reflects the comparison of participant’s response distribution with presented target distribution across the training. In addition, the types of strategy used by participants are also quantified with strategy choice and the strategy integral curve difference (strategy ICD). These variables are further used to examine the rate of change of learning and strategy across training sessions. Detailed calculations of these measures are included in the statistical plan.
